**Figure 1 figure1:**
[figure not shown]
Design of this study. ASH: autosystemic hypnotherapy; SPM: synergetic process management; T1: beginning of the waiting period; T2: at the start of the treatment; T3: at the end of the treatment; T4: at follow-up.

### Ethical Considerations

This study received ethical approval from the Ethics Committee of the Faculty of Psychology and Educational Sciences at Ludwig Maximilian University, Munich (approval number: not specified in protocol; approval letter dated November 8, 2021). The use of the SNS was additionally approved by the Ethics Committee of the Province of Salzburg (No. 415-E/1068/3–2009).

All participants provided written informed consent before the intake assessment (T1). The consent form detailed the study’s purpose, procedures, potential benefits/risks, and data anonymization. Participants were explicitly informed that (1) participation is voluntary and may be withdrawn at any time without consequence, (2) declining or withdrawing imposes no detriment to their clinical care, and (3) no financial compensation or gratuities are offered.

All collected data are subject to data protection regulations and will be published in anonymized form, ensuring participant confidentiality. These procedures are in accordance with the Declaration of Helsinki [42].

### Participants

As this study involves self-assessments via a smartphone application of the SNS, participants are required to have basic smartphone and internet literacy. This is assessed informally during the initial instruction and onboarding process by the respective therapist.

The patients who will be included in this study should be diagnosed with a spectrum of depression and ADs as listed in the *ICD-10* (*International Statistical Classification of Diseases, Tenth Revision*) [43], which is still valid in Germany. These are F32 depressive episode, F33 recurrent depressive disorder, F34 persistent mood disorders, F40 phobic ADs (eg, agoraphobia, social phobia, and specific phobias), F41 other ADs (eg, panic disorder, GAD, mixed anxiety and depressive disorder), F43 reaction to severe stress and adjustment disorders, and F45 somatoform disorders. At least one of these categories should be identified as the main diagnosis; other diagnoses (comorbidities) will be accepted. The reason for focusing on these diagnoses is their high prevalence rates and in consequently, the frequency of occurrence in routine outpatient psychotherapy. Exclusion criteria are aged younger than 18 years, acute suicidality, mental confusion, intoxication by drugs, substance use, and severe neurological diseases.

### Treatment Protocol

This study comprises 2 conditions. One is ASH, which is a version of existing hypno-psychotherapy. It comprises exercises in imagination, activating inner parts (ego-states), and training in mentalization and relaxation. Exercises should induce altered states of consciousness, and triggered ideomotor movements should allow some direct “communication” with “the unconscious.” Resources are activated by the imagination of symbolic persons, figures, or other objects, which might help to protect or support the person to realize changes in their life, to prepare decisions, or to accept and overcome traumatic experiences.

The other condition of this study combines ASH with an advanced method of personalized routine process monitoring, the SPM [44]. The SPM includes (1) an interview for activating personal resources and by this, induces a mental resource state; (2) a method of case conceptualization, which creates a qualitative network model of the most important psychological and social conditions (variables) of a problem [45,46]; and from this, (3) develops a personalized process questionnaire (each item of the questionnaire represents a variable of the model) in close cooperation between the patient and the therapist.

The monitoring is realized by the internet- and server-based device SNS, which collects, stores, analyzes, and visualizes the incoming data from the patient’s smartphone [44]. Patients access the SNS as part of their therapeutic process, supported by their therapist, and use the app in their daily life outside the therapy sessions (ecological setting). No payment is required, and internet access is assumed through patients’ own smartphones. Patients complete one self-assessment per day via the SNS app. They can activate optional reminder notifications in the SNS app to support adherence to daily self-assessments. However, there are no additional prompts such as emails, SMS text messaging, or phone calls from this study’s team.

A final but important part of the SPM is (4) a regular feedback interview on the visualized data of the ongoing process. The feedback interviews take place in standard face-to-face therapy sessions. It can be based on several heuristics, which define important conditions for self-organized pattern transitions to be realized during the change process of a patient, the so-called “generic principles” [44]. The design and functionality of SPM and the SNS are based on the theoretical framework of nonlinear dynamic systems theory applied to psychotherapy. This approach conceptualizes therapeutic change as a self-organizing process characterized by dynamic instabilities, pattern transitions, and emergent reorganization. In the SNS, this framework is operationalized by the continuous self-assessment of individualized process variables, visualized as time series (see Figure 2 for a screenshot of the visualized data in SNS). The system does not rely on standardized change trajectories but allows for the identification of nonlinear phenomena such as phase transitions, critical fluctuations, and synchronization across process dimensions. These visualized patterns are reflected upon during regular feedback interviews and serve as the basis for process-oriented decision-making in therapy. The feedback is thus not triggered by deviations from a normative path (eg, “not on track”) but by the recognition of system-dynamic signals emerging from the individual course of therapy. A recent case study illustrates how ASH with SPM can be integrated [47].

**Figure 2 figure2:**
[figure not shown]
Screenshot of the visualized data in the device SNS. DASS-21: Depression Anxiety Stress Scales – 21 Items; SNS: synergetic navigation system; TPB-R: Therapy Process Questionnaire (German: Therapie-Prozessbogen-Revidiert).

In the ASH+SPM condition, the personalized questionnaire of each patient will be combined with the standardized and validated TPQ [21], both administered at the same sampling rate (once per day).

### Implementation Check

At the end of each session, therapists will estimate to what extent the features and criteria of the respective treatment condition were implemented in the current session. For this purpose, a list of criteria was compiled for each condition. Examples of the ASH criteria are “in this session we applied methods from ASH, like analysis of ambiguity and resistance,” “in this session we activated inner parts (problem or solution-related parts) and archetypes,” “in this session, we used symbolizations,” “in this session, we used metaphors,” “in this session, I supported the patient to apply autosystemic hypnotherapy techniques autonomously.” Examples of the SPM list are “in this session, we reflected the process by using its visualization in the SNS,” “this session was planned and realized with reference to the generic principles,” “in this session, the resources of the patient were important (eg, by conducting a resource interview),” or “in this session, we created a system model or referred to this.” Response options range from “not at all” to “very clearly.”

Beyond these kinds of session ratings by the therapists, regular supervision meetings will be offered to all therapists. These meetings are intended to support the therapists in their work, to reflect on the ongoing process, for example, on difficult situations during the treatments, such as lack of progress and breaks in the alliance, and to obtain an impression from a third-party point of view on which the criteria of the treatment conditions were fulfilled.

### Therapists

All therapists to be included are trained and experienced in ASH, with a professional background in medicine or psychology. All are approbated physicians or psychotherapists according to the German psychotherapy law, with at least some years of practical experience in outpatient psychotherapy. For acquiring competencies in SPM, 8 online training modules on the components of the SPM will be performed, particularly idiographic system modeling and case conceptualization, developing personalized process questionnaires, feedback interviewing, technical handling of the SNS, and understanding and interpreting the diagrams as presented by the SNS. At least 15 therapists will participate in this study, each delivering both conditions.

### Assessments

To evaluate treatment effectiveness, both primary and secondary outcome measures will be assessed at all four measurement points (T1-T4), with participants completing the assessments via online questionnaires in the SNS app outside the therapy sessions.

Primary outcomes focus on symptom reduction in depression and ADs and will be measured using (1) the short version of the Symptom Checklist – 14 Items [48]; and (2) the Depression Anxiety Stress Scales – 21 Items, short version [49,50].

Secondary outcomes include measures of psychosocial functioning, emotion regulation, and quality of life: (1) the General Self-Efficacy Scale [51], (2) the Intercultural Quality of Life Comic [52], and (3) the Difficulties in Emotion Regulation Scale [53,54].

Process and moderator variables will be collected throughout the intervention.

At T2, the motivation for psychotherapy will be measured via a psychotherapy motivation questionnaire (Fragebogen zur Psychotherapiemotivation – 23 Items, FPTM-23) [55] to check for bias between treatment conditions. After each therapy session, the Bern Patient and Therapist Session Questionnaire [56] will assess therapeutic alliance and session quality (therapist and patient reports).

By this, potentially important mediating and moderating variables of the treatment conditions should be incorporated in the analysis, for example, the course of the alliance, the session-by-session micro-outcome, motivation for change, activation of resources, and others.

Additionally, the tool SNS will be used for personalized feedback and monitoring in the ASH+SPM condition, enabling daily assessment of intraindividual change processes based on the TPQ for outpatient psychotherapy [21] in combination with a personalized process questionnaire developed individually with each patient.

### Power Considerations

The estimation of the sample size by power analysis refers to two research questions: (1) Is there a difference between the waiting period and the treatment? (2) Is there a difference between the two conditions of the treatment? The statistical procedure for answering these questions is ANOVA with repeated measures, with the groups (conditions) as the between-subject factor and the comparison of the waiting period (T1-T2, level 1) with the overall treatment (T2-T3, level 2) as the within-subject factor. The power calculation for estimating the sample size was realized by the software package G*Power (Heinrich-Heine-Universität Düsseldorf) [57].

The power estimation of the within-subjects calculation (waiting period versus overall treatment, independent of the condition) was based on the reported average effect size of psychotherapy outcomes from studies included in the meta-analysis (Cohen *d*=0.68) [58]. Using an effect size converter, this d value was transformed into Cohen f (f=0.34), which is needed for calculations in G*Power. The power was defined at 0.95, and the correlation between the measurement points was left at a default value of *r*=0.50. Sphericity was assumed. For two measurement points within the sample, it was estimated that the null hypothesis of no difference (no change) could be rejected with a probability of 96% if a sample size of 32 patients is included.

For the power calculation on the effects of the conditions (between-group comparison), a lower threshold value of the mean effect size was supposed at f=0.25, because of the lack of data in this case. The power was defined at 0.80. All other values and assumptions were the same for the between-subject factor as for the intersubject factor. It was estimated that the null hypothesis of no difference (no change) could be rejected with a probability of 80% if a sample size of 98 patients (49 in each condition) were included.

Based on the estimated sample sizes of 32 patients (hypothesis 1) and 98 patients (hypothesis 2), we defined the overall sample size of this study as 100 patients (n=50 in condition A: ASH; n=50 in condition B: ASH+SPM). The allocation ratio is 1:1 with 50 patients per arm.

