### Aims of This Study

This study addresses different research questions. There is some concern regarding the implementation of the procedure into the routine practice of outpatient psychotherapists, which is challenging because of the complexity of the routine process monitoring procedure. It encompasses an assessment of the patient’s personal resources, a case formulation, and, based on this, the development of a personalized process questionnaire. Regular feedback interviews during the sessions are scheduled with reference to the visualized results. Other research questions focus on the outcome of this study’s conditions and on the patterns of change that may characterize successful or unsuccessful therapies. Potential therapists’ implementation effects will be examined based on an ABAB therapist allocation (see the Study Design section). The main research questions are as follows:

Practicability: Can high-frequency process monitoring (daily self-assessments) and feedback interviewing (at least every second session) be implemented in outpatient routine psychotherapy, that is, in naturalistic settings? To what extent is the routine practice of outpatient psychotherapy supported by process monitoring? What can be learned from this study for the implementation of process monitoring into practice and training?Treatment outcomes: What is the efficacy of ASH compared with a waiting period control? What are the differences in the treatment efficacy of the two randomized implementation conditions, ASH versus ASH supported by personalized process monitoring and feedback in self-reported primary and secondary outcomes?Session effects and change dynamics: What are the differences between the implemented conditions in the experienced quality of the sessions (eg, micro-outcome) and in the therapeutic alliance? Does the process feedback support the therapeutic alliance? With reference to the time series created by the daily self-assessments: Are there specific features of the change dynamics (eg, discontinuous pattern transitions and critical instabilities) related to the outcome?Therapist effects: Are there any differences across therapists (therapist effects)? Is there an interaction between potential therapists’ preferences for a particular implementation condition and outcome?

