## Methods

### Study Design

This study is designed as an RCT with 2 arms, using within-therapist randomization in the real-world clinical practice of routine outpatient psychotherapy in Germany.

Participants are recruited offline through routine intake procedures when presenting for outpatient psychotherapy with participating therapists. Patients who are suspected by the therapist to meet criteria for MDD, AD, or MDD with anxious disorders complex will be briefly screened for their ability and willingness to use a smartphone. If eligible, they will be informed about this study and its requirements by the respective therapist and asked whether they are interested in participating in a research project. Afterward, they will be informed of the procedure and the requirements of this study by the respective therapist. They obtain a flyer with basic information and, in case of concrete interest, will be instructed in detail and obtain an explanation to its full extent.

Patients who have consented to participate in this study will undergo a structured diagnostic interview (Structured Clinical Interview for *DSM-5* [*Diagnostic and Statistical Manual of Mental Disorders* {Fifth Edition}] – Clinician Version) [41] to confirm the inclusion criteria (diagnoses as listed in the Participants section, see below). The interview will be conducted remotely by an independent, trained clinical psychologist who is otherwise not involved in this study. The Structured Clinical Interview for *DSM-5* allows a final decision on including or excluding the patient. In addition to diagnostic confirmation, baseline information on participants’ current medication, concurrent treatment, and symptom severity will be systematically assessed. These variables will be considered as covariates in the main outcome analyses to account for potential prognostic influences. In addition, sensitivity analyses will be conducted to examine whether excluding participants with concurrent treatments or psychopharmacological medication changes affects the robustness of the findings. Following inclusion, a waiting period of 1 (minimum) to 6 months (maximum) begins for each patient, depending on the therapist’s capacity to initiate treatment.

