After the waiting period, a randomization procedure decides on the allocation of a patient to condition A (ASH) or B (ASH+synergetic process management [SPM]). To ensure methodological rigor and internal validity, patients will be randomly assigned to one of the two treatment conditions using therapist-specific block randomization. The predefined block-randomized allocation sequences (eg, ABAB, BABA, AABB, BBAA, ABBA, and BAAB) will be generated in advance by the principal investigator for each therapist to ensure a balanced distribution of conditions within therapists. Patients will be assigned to intervention conditions in the order of study inclusion according to the next position in the respective therapist’s allocation sequence. The allocation sequence will remain concealed from the therapists until each new patient is assigned.

After the randomization, the treatment period starts, whose length depends on the concrete requirements of each patient and must be decided by the patient and therapist together (shared decision-making). In contrast to manualized treatments (adherence to protocol), this is a usual procedure in naturalistic settings. A follow-up assessment will be conducted 6 months after the end of therapy.

There are four assessment points: at the beginning of the waiting period (T1), at the start of the treatment (T2), at the end of the treatment (T3), and at follow-up (T4). The design of this study is illustrated in Figure 1.

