### Statistical Analysis

The statistical procedure for answering the outcome-related questions of this study is ANOVA with repeated measures, with the groups (conditions) as the between-subject factor and the comparison of the waiting period (T1-T2, level 1) with the overall treatment (T2-T3, level 2) as the within-subject factor. The preference ratings of the therapists in the ASH+SPM condition can be used as covariates in a 1-factor ANOVA with repeated measures.

The therapy effects can be predicted by linear regression models and multilevel regression models with conditions, therapy motivation (patients), alliance rates (patients), and the quality of the implementation as predictors. In the ASH+SPM condition, the preference of implementing the SPM (therapists) and the compliance rates (patients) of the process monitoring can also be used as predictors.

The research questions on the dynamics of change (eg, Are pattern transitions related to the outcome?) will be analyzed by applying the Pattern Transition Detection Algorithm [59] and methods of recurrence quantification analysis [60,61]. The respective quantifiers will be correlated with the outcome measures (T2-T3 and T2-T4).

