### Limitations

Despite all the measures taken to optimize the design and minimize biases, there are some limitations due to the naturalistic setting of this study. On the one hand, there are differences in the waiting time, which can be statistically taken into account as covariates in the ANOVA, but cannot be eliminated. The same applies to therapist effects, which can be regarded as a confounding factor, but are not completely eliminated. One reason for this is that it is not yet clear which psychological mechanisms are behind the effects of the therapists, which are more important even in controlled studies than the differences between the treatment conditions [20,36]. Another limitation concerns the implementation check, which is given by self-assessments of the therapists after each session, not by video-based coding of the sessions by independent and blinded raters. Independent session ratings of the quality and the accuracy of the conditions should be realized in future studies, because this can be supposed to have an impact on the outcome, especially in feedback-based therapy sessions.

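### The question about ASH efficacy is tied to a waiting-versus-treatment contrast that pools both arms and is uncontrolled for time, and its 96% power assumes an implausible correlation

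*Protocol article*

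**What the plan says.** **The question.** Aims of This Study asks: "What is the efficacy of ASH compared with a waiting period control". The Introduction (Hypnotherapy and the Concept of ASH) notes that ASH has no controlled efficacy studies so far and says that this project will evaluate it in a controlled design.

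**The contrast.** Statistical Analysis specifies a repeated-measures ANOVA with condition between subjects and "the comparison of the waiting period (T1-T2, level 1) with the overall treatment (T2-T3, level 2) as the within-subject factor". Power Considerations describes the powered effect as "waiting period versus overall treatment, independent of the condition". Allocation is 1:1, 50 patients per arm.

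**The two periods.** Under Study Design, "a waiting period of 1 (minimum) to 6 months (maximum) begins for each patient", with its length set by therapist capacity. Randomization follows the wait. Then "the treatment period starts, whose length depends on the concrete requirements of each patient", decided jointly by patient and therapist. Limitations mentions "differences in the waiting time, which can be statistically taken into account as covariates in the ANOVA". It does not mention treatment length.

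**The power.** A meta-analytic d of 0.68 is used: "this d value was transformed into Cohen f (f=0.34), which is needed for calculations in G*Power". For the correlation, "the correlation between the measurement points was left at a default value of" 0.50. With two levels, the article gives 96% power at 32 patients, against a target of 0.95.

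**The concern.** Three features separate the question from the answer that the plan would produce.

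1. **Which treatment.** The question concerns ASH. The contrast averages over ASH and ASH+SPM, so any benefit of SPM is partly credited to ASH. The trial exists to find out whether SPM adds benefit, so its ASH estimate should not depend on SPM adding none.
2. **What comparison.** All patients wait and all are then treated, in that order, with no concurrent untreated group. The two intervals differ in length within and between patients. Natural course, regression to the mean and elapsed time cannot be separated from treatment.
3. **Which power.** The correlation entered is a software default described as holding between measurement points, but the levels being compared are two changes with T2 in common.

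At stake is what would be the first controlled-efficacy claim for ASH, and a stated power figure that does not belong to the planned contrast.

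**Working it through.** **Step 1: reproduce the 96%.** Inputs from Power Considerations: f=0.34, N=32, m=2 levels, r=0.50, sphericity. Alpha is not stated; 0.05 two-sided is assumed.

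λ = f²·N·m/(1−r) = 0.1156 × 32 × 2 / 0.5 = 14.8, which gives power 0.961. The stated figure reproduces. (Alpha 0.01 gives 0.854 and 0.10 gives 0.983, so 0.05 is the value that fits.)

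**Step 2: the correlation implied for the two levels.** With equal SDs,

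corr(T2−T1, T3−T2) = (r12 + r23 − r13 − 1) / √[4(1−r12)(1−r23)].

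With all three score correlations at 0.50: (0.5 + 0.5 − 0.5 − 1)/√(4 × 0.5 × 0.5) = −0.50. Under an AR(1) pattern the value is −(1−r)/2, or −0.25 at r=0.5. With r12=r23=0.50, a value of +0.50 would need r13=−0.50, the edge of what is admissible.

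**Step 3: power with that correlation.** λ = 7.40/1.5 = 4.93, power 57.5% at N=32. Equivalently, the difference between the two changes has SD √(6−6r) = √3 = 1.73 outcome SDs, so dz = 0.68/1.73 = 0.393. Reaching 95% would take about 87 patients.

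The correlations among T1 to T3 are assumptions, because the article gives only the default. With d=0.68 on the raw SD:

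| Score correlations | Changes correlate | N=32 | Condition A, n=50 | Pooled, N=100 |
|---|---|---|---|---|
| Exchangeable 0.3 | −0.50 | 44% | 63% | 91% |
| Exchangeable 0.5 | −0.50 | 57.5% | 78% | 97% |
| Exchangeable 0.7 | −0.50 | 79% | 94% | 99.9% |
| Exchangeable 0.8 | −0.50 | 92.5% | 99% | >99.9% |
| AR(1) 0.5 | −0.25 | 65% | 85% | 99% |
| AR(1) 0.8 | −0.10 | 98% | 99.9% | >99.9% |

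No dropout is applied.

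**Step 4: pooling.** Half of the treated patients (50/100) receive SPM. The planning effect between arms is f=0.25, so d = 2 × 0.25 = 0.5. If that is the extra T2-T3 change under SPM, the pooled change exceeds the ASH change by 0.5 × 0.5 = 0.25 SD, or 0.25/0.68 = 37% of the planned effect. If SPM adds 0.2 SD, the excess is 0.5 × 0.2 = 0.1 SD.

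**Step 5: elapsed time.** With steady natural improvement of b SD per month, the contrast carries b × (treatment length − waiting length). The article gives neither b nor any therapy length. As an illustration only: a mean wait of 3.5 months, therapy of 6 to 12 months and b of 0.03 to 0.05 give 0.03 × 2.5 = 0.08 to 0.05 × 8.5 = 0.43 SD in favour of treatment. These inputs allow only one sign. For a patient whose therapy is shorter than the wait, the term is negative. Regression to the mean concentrated after T1 would also count against treatment.

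**The case against.** **Pooling is open and the ASH estimate is available.** Power Considerations frames its first question as waiting versus treatment, and the pooled contrast answers that. Condition is a factor in the same ANOVA, so a within-ASH effect could be extracted, and simple effects are often left to an analysis plan. This is fair as far as it goes. But the Aims ask about ASH, and the one contrast that is named and powered answers a different question. That mismatch is in the article itself. The 0.25 SD does rest on an f chosen for lack of data, hence the smaller alternative.

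**The power error changes no decision.** Correct. The sample size comes from the between-arm calculation (98, rounded to 100), and the pooled test keeps about 97% there. A reader might infer that the trial is too small for its pooled contrast; the figures do not support that.

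**The correlation is possible.** A reader might call +0.50 impossible. It is not: r12=r23=0.9 with r13=0.7 is a valid correlation matrix and gives exactly +0.50. It is implausible, and at odds with scores correlating 0.50. With scores correlating 0.8, power at 32 patients returns to 92.5% or 98%, so 57.5% should not be read as the one true value.

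**The article's r may refer to scores.** Then the two levels would be two score occasions, and the calculation would power a plain pre-post test with no waiting comparison, not the contrast described.

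**Time bias need not favour treatment.** A reader might infer that therapy outlasts the wait and so natural recovery inflates the effect. Nothing in the article states a therapy length, so the direction is open. Limitations does acknowledge unequal waiting, but an optional waiting-time covariate does not deal with treatment length.

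**Conclusion.** The point holds in limited form. The contrast that is named and powered does not isolate ASH. The overstatement is 0.25 SD if SPM adds 0.5 SD and 0.1 SD if it adds 0.2 SD. The comparison is an uncontrolled within-patient one, with elapsed time confounded to an unknown extent and in an unknown direction, so it cannot carry a controlled-efficacy claim for ASH.

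The 96% at 32 patients is arithmetically right for its inputs but does not fit two changes that share T2. On the article's own 0.50 between scores it is 57.5%, with a range of 44% to 92.5% (exchangeable 0.3 to 0.8) or 65% to 98% (AR(1) 0.5 to 0.8). The consequence falls on the ASH-only estimate: about 78% at n=50 (63% to 99% over exchangeable 0.3 to 0.8), below the 0.95 target at r=0.5. These figures assume alpha 0.05, equal SDs, d=0.68 on the raw SD and no dropout.

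A reader might also infer that the randomized ASH versus ASH+SPM comparison is compromised. The pooling does not affect it.

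**What to change.** - Answer the ASH question with the period contrast within condition A. Report the pooled contrast separately, labelled as ASH with or without SPM.
- Describe both as uncontrolled within-patient comparisons, and align the wording in the Aims and the Introduction.
- Add a sensitivity analysis that accounts for the lengths of both periods. State that treatment length is chosen by patient and therapist and may depend on response, so scaling to change per month is not a clean correction and should not replace the main contrast. The article does not say that assessment dates are stored; this should be confirmed, although online completion makes it likely.
- Restate the power for the pooled contrast at N=100 and for condition A at n=50, using the correlation implied for the changes and showing a range of score correlations.

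**Cost.** Wording, one prespecified contrast and some analysis code; no further patients or assessments. The price is lower power for the ASH-only estimate and a more modest claim. The Results section reports 22 participants enrolled and no outcome analyses, so the change can still be prespecified.
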